### Interim analyses {21b}

No formal interim analysis has been planned, unless otherwise advised by the Data Safety Monitoring Board (DSMB).

### Methods for additional analyses (e.g. subgroup analyses) {20b}

No subgroup analyses have been planned.

### Methods in analysis to handle protocol non-adherence and any statistical methods to handle missing data {20c}

Patients can have an incomplete course of treatment or data on drug administration may be missing. No imputation of treatment courses will be made for patients with missing data.

### Plans to give access to the full protocol, participant-level data and statistical code {31c}

The dataset will be uploaded on to WWARN and NIMR data server repositories.

## Oversight and monitoring

### Composition of the coordinating centre and trial steering committee {5d}

This is a study coordinated by the ICMR-National Institute of Malaria Research, New Delhi, India with study sites in Kolkata, West Bengal, India and Ahmedabad, Gujarat, India. Study Monitors will be appointed for each site. The monitor will verify the best conduct of the study through frequent contacts by phone and in person with the Principal Investigator and site staff, in accordance with the Standard Operating Procedures and Good Clinical Practice, with the purposes of facilitating the work and obtaining the objectives of the study. These visits will enable the monitor to maintain current, personal knowledge of the study through review of the records, comparison with source documents, observation, and discussion of the conduct of the study with the investigator.

### Composition of the data monitoring committee, its role and reporting structure {21a}

A DSMB will be appointed for this study prior to its initiation. It will have 5-6 members, including a physician, subject experts and a biostatistician. It is responsible for safeguarding the interests of study participants, assessing predominantly the safety of study procedures, and for monitoring the overall conduct of the study.

### Adverse event reporting and harms {22}

The investigator or site staff will be responsible for detecting, documenting and reporting events that meet the definition of adverse events (AEs) or serious adverse events (SAE), and any occurring events will be recorded on the CRF.

#### Definition of AE

Any untoward medical occurrence in a patient or clinical investigation subject, temporally associated with the use of a medicinal product, whether or not considered related to the medicinal product. For marketed medicinal products, this also includes failure to produce expected benefits (i.e. lack of efficacy), abuse or misuse.

The severity of an adverse event is to be scored according to the following scale:Mild: Awareness of sign or symptom, but easily toleratedModerate: Discomfort enough to cause interference with usual activitySevere: Incapacitating with inability to work or perform usual activity

The relationship of an adverse event to study drug is to be assessed according to the following definitions:Definitely unrelated: Should be reserved for those events which occur prior to test drug administration (e.g. washout or single-blind placebo) or for those events which cannot be even remotely related to study participation (e.g. injury caused by a third party).Unlikely: There is no reasonable temporal association between the study drug and the suspected event and the event could have been produced by the subject's clinical state or other modes of therapy administered to the subject.Possible: The suspected adverse event may or may not follow a reasonable temporal sequence from study drug administration but seems to be the type of reaction that cannot be dismissed as unlikely. The event could have been produced or mimicked by the subject's clinical state or by other modes of therapy concomitantly administered to the subject.Probable: The suspected adverse event follows a reasonable temporal sequence from study drug administration, abates upon discontinuation of the drug, and cannot be reasonably explained by the known characteristics of the subject's clinical state.Definitely related: Should be reserved for those events which have no uncertainty in their relationship to test drug administration: this means that a rechallenge was positive.

The outcome of each AE must be assessed according to the following classification:Completely recovered: The patient has fully recovered with no observable residual effectsNot yet completely recovered: Improvement in the patient’s condition has occurred, but the patient still has some residual effectsDeterioration: The patient’s overall condition has worsenedPermanent damage: The AE has resulted in a permanent impairmentDeath: The patient died due to the AEOngoing: The AE has not resolved and remains the same as at onsetUnknown: The outcome of the AE is not known because the patient did not return for follow-up (lost to follow-up)

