## Introduction

### Background and rationale {6a}

In 2021, there were an estimated 247 million cases of malaria from 84 malaria-endemic countries, out of which 4.9 million were caused by *Plasmodium vivax* [1]. India accounted for 79% of cases in the South East Asia (SEA) region and reported approximately 60,000 vivax malaria cases [1]. India along with Pakistan, Papua New Guinea and Ethiopia are the largest contributors to the global vivax burden [1]. There has been a considerable decrease in the malaria burden over the last 6 years since India launched its plan for malaria elimination in 2016; however, case numbers for of vivax malaria remain high. In 2022, the number of cases of vivax malaria increased to 74,126, accounting for 43% of all cases of malaria [2]. If India is to reach its target for malaria elimination in 2030, better strategies will be needed to address the *P. vivax* burden [3].

*P. vivax* is a substantial challenge for malaria control and elimination because of its ability to cause relapsing infections. Relapse results from the activation of dormant liver-stage hypnozoites and can occur weeks or months following an acute infection of vivax malaria [4]. Recurrent infections are associated with a febrile illness, an increased cumulative risk of severe anaemia, direct and indirect mortality, and are an important source of onward transmission of the parasite [4]. The only widely available hypnozoitocidal drug (capable of clearing the intra-hepatic hypnozoites of *P. vivax*) is primaquine. Primaquine is an 8-aminoquinoline compound with the potential of causing severe drug-induced haemolysis in glucose-6-phosphate-dehydrogenase (G6PD) deficient patients. Novel point-of-care tests for G6PD deficiency are now available [5] and they have the potential to facilitate the safer use of primaquine.

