### Outcomes {12}

#### Primary outcomes

##### Efficacy

The incidence risk of symptomatic *P. vivax* malaria at 6 months.A participant will be considered to have demonstrated recurrence-free efficacy at 6 months if:The participant had *P. vivax* asexual parasitaemia at enrolment.The participant has initial clearance of *P. vivax* parasitaemia defined as two negative blood films for asexual P. vivax parasites, with at least 6 h between the counts, and no positive blood films in the interval.The participant was aparasitaemic for asexual *P. vivax* at any assessment following initial parasite clearance.The participant did not take a concomitant medication with anti-malarial activity at any point between the initial study day and their last parasite assessment.The participant is parasite-free at the end of 6 months.

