##### Safety

The proportion of patients vomiting their medication within 1 hour of administration.The proportion of adverse events and serious adverse events.The incidence risk of anaemia (Hb < 8 g/dL) and/or the risk for blood transfusion.Risk of > 25% fall in haemoglobin on any day of treatment.The incidence risk of an acute drop in Hb of > 5 g/dL during primaquine treatment.Gastrointestinal (GI) tolerability — incidence of abdominal pain, heartburn, diarrhoea, constipation, nausea and vomiting.

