### Sample size {14}

The 0.25mg/kg/day × 14 days regimen of primaquine is associated with ~13% recurrence rate of vivax malaria [12]. The present study will assess if 0.50 mg/kg/day for 7 days will have an equivalent recurrence rate within a margin of 10%. A sample size of 200 per group, assuming a 30% loss to follow-up at 5% significance will provide 68% power to detect this difference. Accordingly, we have decided on 200 patients at each site (100 in each arm), 400 in total.

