#### Safety analysis

All safety endpoints will be based on the safety population and presented in tabular and/or graphical format and summarised descriptively.

Clinical laboratory data (clinical chemistry and haematology) will be summarised by the mean, median, standard deviation, minimum and maximum values by treatment group and time point. Laboratory data will also be evaluated by tabulating the number and percentage of subjects in each treatment group with values outside specified threshold values of clinical concern (these may include values outside of the normal range, outer range of clinical concern, and other values of clinical concern).

AE reporting will be performed using the MedDRA (Medical Dictionaries for Regulatory Activities) coding system. Each AE coded using the MedDRA system can be associated with more than one system organ class (SOC). However, for reporting purposes, an AE will be associated with the primary system organ class only. Counting of AEs will be based on the number of subjects — not the number of AEs. For example, if a subject reports the same AE on three occasions within a time interval, that AE will only be counted only once. Subjects reporting more than one AE in a system organ class will only be counted once in that system organ class total. AEs considered by the investigator to have a reasonable possibility of being related to treatment (drug-related AEs) will be summarised by preferred term and SOC. AEs leading to premature withdrawal from treatment and or study will be summarised by preferred term and SOC. AEs that are considered to be gastro-intestinal-related (i.e abdominal pain, heartburn, diarrhoea, constipation, nausea and vomiting) will be summarised. AEs that are considered to be haematologically related (i.e clinically relevant drops in haemoglobin or haematocrit or other complications) will be summarised. Serious adverse events will be summarised by preferred term and SOC. All safety data relating to vital sign variables will be presented as summary statistics (including number, mean, median, interquartile range, standard deviation, minimum and maximum).

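### The adverse event definition takes in lack of efficacy, so P. vivax recurrence also counts in the any-AE safety outcome, and symptoms of late recurrences count in GI tolerability

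*Protocol article*

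**What the plan says.** All references are to the protocol article.

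- **Definition of AE.** The opening sentence takes in any untoward occurrence in a patient, related or not. The next adds: "For marketed medicinal products, this also includes failure to produce expected benefits (i.e. lack of efficacy), abuse or misuse".
- **Adverse event reporting and harms {22}.** Site staff must detect, document and report whatever meets the AE or SAE definition, and occurring events go on the CRF.
- **Participant timeline {13}, Table 1.** The AE/SAE row is marked from Day 0 through month 6 and again in the day-of-recurrence column.
- **Outcomes {12}, Safety.** One outcome is "The proportion of adverse events and serious adverse events". Another is GI tolerability, a list of six symptoms that includes nausea and vomiting and carries no time window.
- **Outcomes {12}, Efficacy.** The primary outcome is "The incidence risk of symptomatic *P. vivax* malaria at 6 months". The abstract instead names any parasitaemia, which the Outcomes section makes secondary.
- **Safety analysis.** AEs are counted by subject and safety is summarised descriptively. "AEs considered by the investigator to have a reasonable possibility of being related to treatment (drug-related AEs) will be summarised" by preferred term and system organ class, as are SAEs.

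No section shown separates recurrences or their symptoms from AEs.

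**The concern.** The benefit expected of primaquine in this trial is prevention of recurrence. The background calls it "The only widely available hypnozoitocidal drug", so it is safe to infer that it is a marketed product, although the article does not use that word for it. A recurrence is then a failure of expected benefit, hence an AE by definition, and it must be recorded at any time up to month 6.

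The efficacy event therefore feeds a stated safety outcome. The second objective compares the safety and tolerability of the two regimens. An arm with more recurrences would show a higher any-AE proportion even if the drug did no more harm, and an arm with fewer would show a lower one.

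GI tolerability is exposed in a similar way. The haemoglobin-fall outcomes are tied to the treatment period, but GI tolerability is not. Nausea during a month-4 recurrence would count against a 7-day or 14-day course that ended months earlier.

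**Working it through.** The plan gives no figure for this overlap, so there is none to reproduce. The check has two parts: which tables a recurrence enters, and how far it could move the any-AE proportion.

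**Which tables a recurrence enters**

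| Table or outcome | Condition for entry | Does a recurrence enter? |
|---|---|---|
| Any AE | Meets the AE definition | Yes. A symptomatic one enters under the opening sentence alone, and an asymptomatic one through the lack-of-efficacy clause |
| Drug-related AE | "AEs considered by the investigator to have a reasonable possibility of being related to treatment" | Only if the investigator judges it so |
| SAE | One of the listed seriousness criteria, such as hospital admission | Only if one is met. Lack of efficacy is not listed |
| GI tolerability | One of the six listed symptoms | Only through nausea, vomiting or another listed symptom. Fever is not listed |
| Vomiting within 1 hour of a dose; haemoglobin falls during treatment | Tied to dosing or treatment days | Not affected by the clause |

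**Size of the effect on the any-AE proportion**

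Inputs:
- Control recurrence 13% (Sample size {14}: the standard regimen "is associated with ~13% recurrence rate of vivax malaria").
- Margin 10%, read as absolute, so the unfavourable case is 13% + 10% = 23%.
- 200 per arm, and 200 × 0.70 = 140 after the stated 30% loss.
- Background proportion *b* with some other AE: not in the document. I assume 20% to 40%, independent of recurrence.

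Patients who become AE cases through recurrence:
- At 13%: 200 × 0.13 = 26 per arm, or 140 × 0.13 = 18.2 among the evaluable.
- At 23%: 200 × 0.23 = 46, or 140 × 0.23 = 32.2.

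With recurrence risk *r*, the any-AE proportion is 1 − (1 − b)(1 − r).

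| b | r = 13% | r = 23% | Gap |
|---|---|---|---|
| 20% | 1 − 0.80 × 0.87 = 30.4% | 1 − 0.80 × 0.77 = 38.4% | 8.0 points |
| 40% | 1 − 0.60 × 0.87 = 47.8% | 1 − 0.60 × 0.77 = 53.8% | 6.0 points |

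In general the gap is (1 − b)(r₁ − r₀). Over a wider range of *b* it is 0.90 × 10 = 9 points at b = 10% and 0.50 × 10 = 5 points at b = 50%.

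At equal recurrence the gap is zero. The level still rises in both arms, by (1 − b) × 13%: 10.4 points at b = 20% and 7.8 points at b = 40%.

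**The case against.** The clause is generic definition text, and an article condenses a longer protocol. How endpoint events are handled in AE tables is often left to the SAP or CRF instructions, which are not shown. This limits the weight of the point but does not remove it. The issue is not a missing rule. The article states a rule that brings efficacy failure into AE recording, and nothing shown takes it out again.

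A reader might go further and infer that every recurrence lands in the drug-related and SAE tables, so that an efficacy difference would read as a safety difference throughout. The documents do not support that. Relatedness is the investigator's judgement. Of the upper categories, probable needs the event to abate on stopping the drug and definite needs a positive rechallenge, and neither fits a relapse after the course has ended. An uncomplicated recurrence managed without admission would meet no seriousness criterion. For the same reason it does not follow that the drug-attributable AE rate is overstated, because the any-AE count does not measure that rate.

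Three further limits stand:
- Safety is descriptive, with no stated test between arms.
- In tables by preferred term a recurrence could appear on its own line, where a careful reader would see it. That does not correct the overall proportion.
- The 6-8 point gap needs a true recurrence difference equal to the full margin, together with assumed background rates.

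**Conclusion.** The point holds for the any-AE proportion and, through symptoms of late recurrences, for GI tolerability. It holds for the drug-related and SAE tables only in cases judged related or serious. Outcomes tied to dosing or to treatment days are not touched by the clause.

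The any-AE proportion could differ by 6-8 points with identical toxicity. This assumes 13% v 23% recurrence, every recurrence recorded as an AE, and an independent 20-40% background AE rate. The gap shrinks with the recurrence difference and vanishes when recurrence is equal. The weight is moderate: the primary analysis is unaffected, but a listed safety outcome in a trial meant to inform national guidelines would partly measure efficacy.

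**What to change.** Add to the AE definition, and carry into the Safety analysis section, wording such as: *Recurrent P. vivax parasitaemia and the signs and symptoms attributed to it are efficacy outcomes and are tabulated separately from adverse events. A recurrence that meets a seriousness criterion is still reported as an SAE and is shown on its own line.* Then:

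- Present the any-AE and GI totals with and without recurrences and their attributed symptoms.
- Summarise GI tolerability over the same fixed early window in both arms.

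Two simpler remedies do not work. Deleting the lack-of-efficacy clause leaves symptomatic recurrence inside the opening sentence of the definition. Counting only AEs that begin before recurrence shortens observation in the arm with more recurrences, so efficacy would again drive the count.

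The cost is a few sentences, a filter in the tables and a mark on the CRF for symptoms attributed to recurrence. Recurrence dates are already needed for the time-to-event analysis. The headline AE count becomes smaller. Deciding which symptoms belong to a recurrence is a judgement by unblinded staff, and the with-and-without display makes its effect visible.

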#### Definition of SAE

A serious adverse event (SAE) is any untoward medical occurrence that, at any dose:Results in deathIs life-threateningRequires hospitalisation or prolongation of existing hospitalisationResults in disability/incapacityIs a congenital anomaly/birth defectRequires intervention to prevent permanent impairment or damage

In the event of an SAE, the site investigator will report the case to the sponsor and chairman of the ethics committee (EC) within 24 h of its occurrence. The report of SAE will then be forwarded by the principal investigator to chairman of EC within 14 days of its occurrence. Trial participants who suffer direct physical, psychological, social, legal or economic harm as a result of participating in the trial are entitled to free health care and referrals as needed. Where any death of a participant occurs during the clinical trial, the legal heir of the trial subject shall be provided financial compensation by the National Institute of Malaria Research (NIMR-New Delhi) through insurance coverage.

The EC is responsible for reviewing the relatedness of the SAE to the research, as reported by the researcher, and determining the quantum and type of assistance to be provided to the participants. All research participants who suffer harm, whether related or not, should be offered appropriate medical care, psycho-social support, referrals, clinical facilities, etc. Medical management should be free if the harm is related to the research. Compensation should be given to any participant when the injury is related to the research. This is applicable to participants in any of the arms of research, such as intervention, control and standard of care. The quantum of compensation to be awarded to participants who have suffered research-related injury, the EC will consider aspects including the type of research (interventional, observational, etc.), extent of injury (temporary/permanent, short/long term), loss of wages, etc.

All the patients enrolled in the study will be reimbursed for their daily wage loss and transportation.

### Frequency and plans for auditing trial conduct {23}

A detailed monitoring plan is prepared. In brief, this will state that a minimum of four in-person monitoring visits will be conducted during the course of the study.

Monitoring frequency may be increased based on the following criteria among others: (i) high subject enrolment at a particular site; (ii) compliance issues (e.g. significant protocol violations); (iii) site staff turnover, requiring additional training; (iv) results and findings from previous monitoring visit.

Auditing can also take place by national health authorities at the participating study sites.

### Plans for communicating important protocol amendments to relevant parties (e.g. trial participants, ethical committees) {25}

All protocol modifications will be communicated promptly to all involved parties and updated in the clinical trials registry. Any protocol deviations will be fully documented.

### Dissemination policy {31a}

Results will be published in peer-reviewed journals. All investigators will be involved in reviewing drafts of the manuscripts, abstracts, press releases, and any other publications arising from the study. Authorship will be determined in accordance with the ICMJE guidelines and other contributors will be acknowledged. Results will further be disseminated at international conferences and other stakeholder meetings including the National Centre for Vector Borne Disease Control in India. All efforts will be made to disseminate results to study participants in line with local requirements.

## Discussion

India aims to eliminate malaria by 2030. One of the major challenges to achieve this goal is the radical cure of patients with *P. vivax* malaria. The latter can be undermined by long treatment courses, resulting in poor adherence and reduced effectiveness. Shorter treatment options have now been recommended by WHO^7^ but additional local evidence of their efficacy and safety are required for the Indian malaria program to inform implementation and change policy. Earlier studies [11, 12, 14] did not generate enough evidence for policy change. This study will directly inform treatment policy.

## Trial status

Started

Protocol number: NIMR-IDDO/PQ/2022-01

Version number and date: Version 03, Date-14/03/2023

Recruitment start date: 11/9/23

Estimated date of completion of recruitment: Mar. 2024

## Abbreviations

AE: Adverse event
AMM: Adjusted male median
CTRI: Clinical Trial Registry of India
CQ: Chloroquine
DSMB: Data Safety Monitoring Board
EC: Ethics Committee
G6PD: Glucose-6-phosphate dehydrogenase
ICMR: Indian Council of Medical Research
NCVBDC: Indian National Center for Vector Borne Diseases Control
NIMR: National Institute of Malaria Research
PQ: Primaquine
SAE: Severe adverse event
WHO: World Health Organization
